### Mortality

Mortality during the first 12 months following surgery will be collected from NHS spine (NHS Digital; https://digital.nhs.uk/).

### Resource use

Case report forms will be used to collect resources from medical records during the initial inpatient stay, and post discharge for 12 months at the treating hospital. Further resource use will be collected from the participants to complement the medical records. Participant questionnaires will be administered by telephone or post. They will enquire about hospital contacts related to the index fracture with hospitals other than the index treating sites, rehabilitation units and other care settings. Questions will also ask about the use of equipment and changes to the home, private expenses with rehabilitation services, informal care and loss of productivity.

### Sample size

The sample size for this study is 1128 participants. This full trial sample size is based on the SD of the EQ-5D-5L at 4 months post surgery of 0.3 points^31^ and a minimal clinically important difference of 0.075^39^ with 2-sided significance of 5% requiring 506 with the primary outcome for 80% power or 676 with the primary outcome for 90% power.

In this population, we expect considerable loss to follow-up. Previous WHiTE trials have indicated that these losses are due mainly to patients declining consent to further follow-up, incapacity, and death.^40 41^ We are able to account for participants who have died in our primary outcome measure and have assumed that only 60% of recruited study participants will be available at the definitive endpoint at 4 months.

With a significance level of 5%, this inflates the sample size to 844 for 80% power and 1128 for 90% power. Conservatively, we aim to randomise 1128 in order to ensure a minimum of 676 participants with the primary outcome which will ensure 90% power based on these assumptions.

Similar sample size calculations have been used in existing clinical trials in this patient population (ISRCTN92825709, ISRCTN18393176).

### Statistical analysis

A full, detailed statistical analysis plan (SAP) will be drafted early in the trial and will be finalised following the recruitment review by the Data and Safety Monitoring Committee (DSMC) and Trial Steering Committee (TSC), and prior to the primary analysis data lock. Any subsequent changes to the SAP will be fully justified in the final report.

Baseline demographic data will be summarised to check comparability between treatment arms. Standard statistical summaries and graphical plots will be presented for the primary outcome measure and all secondary outcome measures.

The study analysis will use generalised mixed-effect regression models, with all analyses adjusting for important baseline covariates to improve precision in estimation of the treatment effect. The principal analyses will be conducted on the intention-to-treat population. Differences between intervention arms for the primary outcome measure, EQ-5D-5L^33^ scores at 4 months post surgery, will be analysed by calculating an adjusted treatment effect using a mixed-effect linear regression. A zero value will be imputed for participants who have died prior to this time point. Models will adjust for age, sex, fracture type and cognitive impairment (as fixed effects) and recruitment centre as a random effect to take account of the heterogeneity in the response between centres. The treatment difference will be estimated from the fitted model, together with 95% CIs, with significance set at 5% (2-sided) for comparative tests.

A sensitivity analysis will be performed on a per-protocol (as treated) basis. Further sensitivity analysis of EQ-5D-5L^33^ at 4 months with additional adjustment for the retrospective preinjury baseline EQ-5D-5L^33^ will be carried out to enable the influence of this factor to be evaluated.

Secondary clinical outcomes will be similarly analysed with logistic mixed-effect regression being used for binary data and linear mixed-effect regression for continuous data.

Adverse events will be explored to assess if they differ between groups.

Stata (StatCorp, LP) or other appropriate validated statistical software will be used for all analysis.

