## Abstract

**Introduction:**

People who sustain a hip fracture are typically elderly, frail and require urgent surgery. Hip fracture and the urgent surgery is associated with acute blood loss, compounding patients’ pre-existing comorbidities including anaemia. Approximately 30% of patients require a donor blood transfusion in the perioperative period. Donor blood transfusions are associated with increased rates of infections, allergic reactions and longer lengths of stay. Furthermore, there is a substantial cost associated with the use of donor blood. Cell salvage and autotransfusion is a technique that recovers, washes and transfuses blood lost during surgery back to the patient. The objective of this study is to determine the clinical and cost effectiveness of intraoperative cell salvage, compared with standard care, in improving health related quality-of-life of patients undergoing hip fracture surgery.

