Concerns regarding patient safety and the costs of allogenic blood have driven efforts to reduce transfusion rates.^16^ Intraoperative cell salvage is a method of collecting blood lost during surgery with an option of transfusing it back to the patient. The cell salvage device filters, washes and centrifuges blood lost during surgery, to separate the red blood cells from non-cellular matter prior to intraoperative autotransfusion. Complications as a result of cell salvage are rare.^15^

In order to reduce the use of allogenic blood, the NICE guidelines (Blood Transfusion NG24 2015) recommended the use of cell salvage and tranexamic acid where surgical blood loss is expected to be greater than 500mls.^17^

The direct intraoperative blood loss reported across studies of hip fracture surgery is variable.^18–21^ Several randomised controlled trials report a mean intraoperative blood loss greater than 500 mL in patients undergoing different types of surgery for a fractured hip.^22–25^ When intraoperative losses are added to blood lost as a direct result of the fracture, the total blood loss is estimated to be between 550 ml-1300mL.^9^

When considering whether to use cell salvage, patients with a hip fracture present a unique population. They have a high mortality, high transfusion rates and high degrees of pre-existing morbidity including anaemia. These considerations mean that there are large potential benefits of using cell salvage in this population. Using cell salvage to reduce the use of allogenic blood has the potential benefit to patients of improving their outcomes from hip fracture surgery, by reducing infections, length of stay and levels of anaemia.

It is currently routine practice to use a restrictive transfusion policy in hip fracture surgery, but the use of cell salvage has not become embedded in this patient group. We propose evaluating the clinical and cost effectiveness of cell salvage and autotransfusion in hip fracture surgery.

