### Treatments

#### Preoperative assessments

Diagnosis of a hip fracture will be confirmed by a plain radiograph, as per routine clinical care. Routine investigations, anaesthetic assessment, antibiotic and venous thromboembolic prophylaxis will be used as per local policy.

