#### Trial treatments

All participants will receive perioperative prophylactic antibiotics in accordance with current protocols agreed at each centre. Appropriate preparation, positioning and fracture reduction will be left to the discretion of the operating surgeon, as per their normal clinical practice. The need for allogenic blood products will be determined on an individual patient basis, following each centre’s blood transfusion policy. This will typically involve restrictive transfusion thresholds where asymptomatic patients with a haemoglobin concentration of less than 70 g/L are offered allogenic blood. This threshold may be higher, typically a haemoglobin concentration of less than 80 g/L in those with symptomatic anaemia or coexisting cardiorespiratory disease.

Participants will be randomly allocated to one of the treatment arms:

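### The covariate list written for EQ-5D-5L is carried over to allogenic blood use without preoperative haemoglobin, which costs precision and power on that secondary outcome

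*Protocol article*

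**What the plan says.** The Statistical analysis section of the protocol article says that all analyses adjust for important baseline covariates in order to gain precision. In the paragraph on the primary outcome it names them: "Models will adjust for age, sex, fracture type and cognitive impairment (as fixed effects) and recruitment centre as a random effect". Secondary clinical outcomes are then to be treated in a similar way, with logistic mixed models for binary data and linear mixed models for continuous data. The only other covariate mentioned is retrospective pre-injury EQ-5D-5L, in a sensitivity analysis of the primary outcome. Randomisation is stratified by fracture type and centre only.

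Allogenic blood use in the index admission is a stated secondary objective, with units and dates taken from blood bank records. The Abstract puts the background rate as follows: "Approximately 30% of patients require a donor blood transfusion in the perioperative period". Under Trial treatments, the typical restrictive policy is that "asymptomatic patients with a haemoglobin concentration of less than 70 g/L are offered allogenic blood". The level may be higher, typically 80 g/L, with symptoms or cardiorespiratory disease, and the decision is individual and follows centre policy. The Introduction says that fracture and surgical blood loss worsen anaemia already present, and that cell salvage could help patients "by reducing infections, length of stay and levels of anaemia". On work-up before surgery, the article says: "Routine investigations, anaesthetic assessment, antibiotic and venous thromboembolic prophylaxis will be used as per local policy".

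**The concern.** The named covariates suit a quality-of-life score. Carried over to donor blood use, they leave out the baseline measurement that the article's own account ties most directly to that outcome. Donor blood is offered according to haemoglobin, and the level reached depends on where the patient starts and how much blood is lost. Neither the stratification nor the described model takes account of the starting level.

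Allogenic blood use is the outcome closest to the intervention, and reducing it is part of the route by which the Introduction expects patients to benefit. If quality of life does not differ between arms, the blood result will help readers judge whether cell salvage did what it was meant to do. A wider interval than necessary makes that judgement harder.

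**Working it through.** **The plan's own figures.** Inputs from Sample size and Statistical analysis: SD 0.3 ("based on the SD of the EQ-5D-5L at 4 months post surgery of 0.3 points"), difference 0.075 ("a minimal clinically important difference of 0.075"), two-sided 5%, and 60% available at 4 months. The normal approximation, n per arm = 2(z₀.₉₇₅ + z_power)²(0.3/0.075)², gives 337 for 90% power and 252 for 80%. The noncentral-t version gives 338 and 253, so 676 and 506 in total, as stated. Dividing by 0.6 per arm: 338/0.6 = 563.3, rounded up to 564, so 1128; 253/0.6 = 421.7, rounded up to 422, so 844. Both match. There is no arithmetic error, and no sample size or power is stated for allogenic blood.

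**Effect of adding a covariate.** Let R² be the share of outcome variance that haemoglobin explains beyond the listed covariates. The documents give no value, so 0.10 to 0.30 is an assumption. In a linear model the SE is multiplied by √(1 − R²), and the effective sample size by 1/(1 − R²):

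- R² = 0.10: √0.90 = 0.949, SE about 5% smaller; 1/0.90 = 1.11
- R² = 0.20: √0.80 = 0.894, about 11% smaller; 1/0.80 = 1.25
- R² = 0.30: √0.70 = 0.837, about 16% smaller; 1/0.70 = 1.43

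**On the risk-difference scale.** Take 564 per arm (assuming blood bank data for all randomised), 30% transfused as in the Abstract, and the two-sided 5% level. Without haemoglobin, SE = √(2 × 0.3 × 0.7/564) = 0.0273. The transfusion rate under cell salvage is not given; 23% is assumed for illustration. Power uses n/(1 − R²) in the two-proportion formula.

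| R² | SE of risk difference | Power, 30% vs 23% | Difference detectable at 80% power |
|---|---|---|---|
| 0 | 0.0273 | 76.0% | about 7.4 points |
| 0.10 | 0.0259 | 80.2% | 7.0 points |
| 0.20 | 0.0244 | 84.6% | 6.6 points |
| 0.30 | 0.0228 | 89.0% | 6.2 points |

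The power gain depends on the assumed effect. For 30% vs 27%, power rises only from 19.9% to 26.6% at R² = 0.30; for 30% vs 20% it is already 97.3% without haemoglobin.

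**Logistic model and validity.** A simulation used N = 1128, about 30% vs 23%, transfusion when the lowest haemoglobin falls below a cut-off, and assumed haemoglobin SDs. The models held treatment alone, or treatment plus preoperative haemoglobin, so R² here is total and not incremental. Where haemoglobin explained about 12%, 21% and 33% of the variance, logistic power rose from about 75–76% to 82%, 85% and 92%, and the linear-model SE fell by 6%, 11% and 18%. With no treatment effect, rejection was about 4–6% with or without haemoglobin (500 runs per scenario). The omission costs efficiency and does not damage validity.

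**The case against.** The strongest reply is that covariates for individual secondary outcomes normally belong in the full SAP, which is announced but not shown. The list stands in the paragraph on the primary outcome and reaches secondary outcomes through a clause mainly about model type. This stands in part: a reader might infer that haemoglobin will enter no model, but the article supports only that it enters none described there. The point survives because the article does not merely leave the matter open. It names a list and extends it.

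Other stronger readings also fail.

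- **That preoperative haemoglobin settles who is transfused.** The thresholds concern haemoglobin when transfusion is considered. That level also reflects blood loss, and the threshold varies with symptoms, comorbidity and centre policy. Fracture type and centre are already in the model. No strength of association is given.
- **That recruitment should have been restricted to patients likely to need blood.** Broad enrolment is a deliberate pragmatic choice with a quality-of-life primary outcome, there are four exclusion criteria, and adjustment has no bearing on it.
- **That the comparison is biased.** Randomisation protects it. Chance imbalance in haemoglobin is already reflected in the unadjusted interval and is not a second harm.
- **That a treatment-by-haemoglobin interaction is needed.** It would add an unpowered test to a secondary outcome.

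Two technical objections stand and limit the claim. The gain depends on what haemoglobin adds beyond the listed covariates, and the SE formula belongs to a linear model. In a logistic model, adjustment changes the odds ratio being estimated and need not shrink the SE of its logarithm.

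**Conclusion.** The point holds as a minor, inexpensive improvement. For allogenic blood use, the described model omits a plausible strong predictor although the article's stated purpose in adjusting is precision. Under an assumed incremental R² of 0.10 to 0.30, the avoidable loss is about 5% to 16% in the SE of a linear model of units or of a risk difference. For a binary transfusion outcome analysed by logistic regression, the loss is one of power. The R² range, the effect on transfusion and the simulated haemoglobin SDs are all assumptions; the direction does not depend on their exact values provided haemoglobin adds some prediction. No power is claimed for this outcome, so no stated figure becomes wrong.

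**What to change.** Extract one routine pre-randomisation haemoglobin per participant from the hospital laboratory record. The first value on admission is preferable: units are counted over the whole index stay, so a transfusion before surgery could be part of the outcome and also raise a later preoperative value. Prespecify it as a continuous fixed effect in the allogenic-blood models, in addition to the existing list, before the primary analysis data lock. Impute missing baseline values simply, for example by the overall mean without using allocation or outcome. If the outcome is analysed by logistic regression, state that the odds ratio is conditional on haemoglobin.

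The cost is one further value to extract per participant, a few missing values and a line of analysis wording. No new blood test should be needed, assuming that haemoglobin is among the routine investigations, which the article does not list. If the SAP already includes this covariate, no change is needed.

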### Cost-effectiveness analysis

A within-trial cost-effectiveness analysis will be conducted from the UK NHS and Personal Social Services perspective^42^ in the base case analysis. Resource utilisation involving cost of the cell salvage and autotransfusion if applicable will be obtained from case report forms (CRFs) that will be completed by the local research teams. Broader resource utilisation will be captured through CRFs and patient questionnaires administered at baseline, 4 months, and 12 months post surgery. Unit costs for health and social care resources will largely be derived from the latest available local and national sources and estimated in line with best practice. Costs will be standardised to current prices where appropriate. An incremental cost-effectiveness analysis, expressed in terms of incremental cost per quality-adjusted life year gained, will be performed. Results will be presented using incremental cost-effectiveness ratios, net monetary benefit, and cost effectiveness acceptability curves generated via non-parametric bootstrapping. Multiple imputation methods will be used to impute missing data and avoid biases associated with complete case analysis. Sensitivity analyses involving economic analysis from the societal perspective and extending the time frame from 4 months to 1 year will also be conducted.

### Trial organisation and oversight

The sponsor of this trial is University Hospitals Coventry and Warwickshire NHS trust. The day-to-day management of the trial will be the responsibility of the trial manager, based at the University of Oxford and supported by OCTRU staff. This will be overseen by a trial management group, who will meet monthly to assess progress. It will be the responsibility of the trial manager to undertake training of the research associates at each of the study centres. The study statistician and health economist will be closely involved in setting up data capture systems, design of databases and clinical reporting forms.

A TSC and an independent DAMOCLES^43^ compliant DSMC, that will assess progress, conduct and participant safety, will be set up at the start of the study.

### Quality control

Quality control procedures will be undertaken during recruitment and data collection phases of the study to ensure research is conducted, generated, recorded and reported in compliance with the protocol, GCP and ethics committee. The chief investigators and the trial manager will develop data management and monitoring plans.

### Patient and public involvement

At the centre of this trial is the potential for patient benefit by reducing the risks of hip fracture surgery and improving patient outcomes. The study proposal was discussed with our panel of 15 patient and public members. A member of this panel is a coapplicant on this trial and helped draft the protocol, lay summary and patient information sheet. A lay summary informing patients and the public of the trial outcome will be available on the trial website. Further documentation suitable for the general patient and public communities will be prepared by the research team in collaboration with lay representatives.

### Ethics and dissemination

This study will be embedded within the WHITE portfolio of trials. NHS ethical approval was provided on 14/08/2019 (19/WA/0197) and the trial registered (ISRCTN15945622). The results of this trial will be disseminated to the hip fracture clinical community via presentations at national and international meetings as well as publication in peer-reviewed journal. Results will be disseminated in lay form to participants and the public.
